## Abstract

**Background:**

Venous leg ulceration is a common and costly problem that is expected to worsen as the population ages. Current treatment is compression therapy; however, up to 50 % of ulcers remain unhealed after 2 years, and ulcer recurrence is common. New treatments are needed to address those wounds that are more challenging to heal. Targeting the inflammatory processes present in venous ulcers is a possible strategy. Limited evidence suggests that a daily dose of aspirin may be an effective adjunct to aid ulcer healing and reduce recurrence. The Aspirin in Venous Leg Ulcer study (ASPiVLU) will investigate whether 300-mg oral doses of aspirin improve time to healing.

**Methods/design:**

This randomised, double-blinded, multicentre, placebo-controlled, clinical trial will recruit participants with venous leg ulcers from community settings and hospital outpatient wound clinics across Australia. Two hundred sixty-eight participants with venous leg ulcers will be randomised to receive either aspirin or placebo, in addition to compression therapy, for 24 weeks. The primary outcome is time to healing within 12 weeks. Secondary outcomes are ulcer recurrence, wound pain, quality of life and wellbeing, adherence to study medication, adherence to compression therapy, serum inflammatory markers, hospitalisations, and adverse events at 24 weeks.

**Discussion:**

The ASPiVLU trial will investigate the efficacy and safety of aspirin as an adjunct to compression therapy to treat venous leg ulcers. Study completion is anticipated to occur in December 2018.

**Trial registration:**

Australian New Zealand Clinical Trials Registry, ACTRN12614000293662

## Background

Venous leg ulcers (VLUs) are a common and costly problem, usually managed in general practice and community settings with variability in clinical practice [1]. Age-related venous leg ulceration is the most common cause of lower limb ulceration in developed countries, with an overall prevalence between 1.65 and 1.74 % and substantially higher rates in adults of age 65 and older [2]. These ulcers become chronic due to the underlying pathophysiology and are associated with pain and heavy exudate [3]. In 2010, an estimated 400,000 Australians were treated for VLUs, translating into costs of more than AU$3 billion per year [4]. People with chronic venous insufficiency (CVI) are prone to developing VLUs on the lower legs, which can occur spontaneously or after minor trauma [5]. Up to 70 % of VLUs will heal within 12 weeks if adequate compression is applied and patients adhere to compression treatment [6]. People with VLUs also often suffer from diabetes and obesity, further impacting the healing [7]. The natural history of ulceration is a cycle of healing and recurrence, which has considerable impact on an individual’s health, quality of life, and socioeconomic costs [8, 9]. Increasing life expectancy means that more people will be living with VLUs in the future, increasing the financial and healthcare burden of this already costly chronic disease [10, 11].

### Current treatment of venous leg ulcers

Best practice VLU treatment is a firm graduated compression bandage to aid venous return [12]. This assists by reducing venous hypertension, enhancing venous return, and reducing peripheral oedema. Data shows that VLUs heal more quickly with compression than without [12]. Treatment inconsistencies regarding the bandage application and limited patient adherence to compression therapy have been identified as limiting factors to healing [1]. Many healed ulcers recur within 3 months of healing, possibly due to a prolonged inflammatory response [6]. Aspirin is a widely used and relatively well-tolerated drug. It has the potential to reduce inflammation via generalised COX inhibition.

Classical signs of inflammation have been observed in biopsies and plasma samples in experimental models of venous disease [13], and evidence supports the hypothesis that, in humans, chronic venous disease is associated with the inflammatory cascade [14]. The cascade begins with increased vascular permeability and progresses to the adhesion of leukocytes and platelets to the endothelium. Over time, increased cell apoptosis, degradation of the basement membrane and extracellular matrix proteins, and vascular restructuring of the venous varicosities occurs [15]. High-level evidence shows larger wounds of longer duration (>10 cm^2^ and > 12 months old) at the first visit have only a 20 % chance of healing by the 24th week of care, whereas a wound that is smaller than 10 cm^2^ and has been present for less than 12 months has a better (70 %) chance of healing by 24 weeks [10, 16]. A perpetual inflammatory state may contribute to difficult-to-heal chronic wounds [17]. VLUs may achieve better healing and be less likely to occur due to anti-inflammatory effects if the compression bandage is used concomitantly with aspirin [18].

### Aspirin as a novel treatment in VLUs

Aspirin has several actions potentially capable of influencing the progression of VLUs through the suppression of inflammation. It inhibits the enzyme cyclooxygenase (COX), thereby blocking the synthesis of several potent stimulators of inflammation [19]. In vivo studies suggest that 300 mg aspirin suppresses inflammatory markers and may promote ulcer healing [20]. Aspirin also reduces prostaglandin-2 and thromboxane A2, which are involved in platelet aggregation [19]. The production of these compounds underpins part of the anti-inflammatory effect of aspirin, along with the potential to inhibit both leukocyte activation and platelet function [18]. The effect of low-dose aspirin on serum levels of inflammatory cytokines, such as interleukin 6 (IL-6) and tumour necrosis factor-alpha (TNF-a), is not entirely clear at present. In one study of aspirin in people with VLUs, investigators reported increased fibrinogen and an increased coagulation rate, which increased the healing rates [21]. Some publications report little or no effect on the serum levels of pro-inflammatory cytokines, while others show reduced serum IL-6 and TNF-a with 2 weeks treatment using 300 mg/day aspirin [20].

### Previous studies of aspirin in venous leg ulcers

Two small, randomised, controlled trials (RCTs) suggest aspirin may be effective in speeding ulcer healing and may reduce the ulcer recurrence, although the quality of this evidence is low. An RCT conducted in the United Kingdom [21] (*n* = 20) reported that daily oral administration of aspirin (300 mg) with compression decreased the time to ulcer healing (*p* < 0.01) and the proportion of participants healed when compared to placebo with compression bandaging over a 4-month period. Thirty-eight per cent of the aspirin participants reported complete healing compared with 0 % in the placebo group (*p* < 0.007). Improvement, assessed by a reduction in wound size, occurred in 52 % of the aspirin group compared with 26 % with placebo (*p* < 0.007). The potential benefits of aspirin as an adjunct to compression were identified, but the sample size was small, and the mechanism by which aspirin improved healing or the effect on recurrence was not reported [20]. A more recent Spanish RCT [22] (*n* = 51) compared daily administration of aspirin (300 mg) in addition to the use of a compression bandage with compression alone over a 5-month period [22]. Little difference was observed in the complete healing between the groups (21/28 aspirin and 17/23 compression alone); however, the average time to healing was shorter (12 weeks in the aspirin group versus 22 weeks in the compression-only group), and the average time to recurrence was longer in the aspirin group (39 days (SD 6.0) for aspirin versus 16.3 days (SD 7.5) for compression alone). No information regarding the placebo was reported.

The ASPiVLU study in Australia will investigate the effects of aspirin in people with VLUs in a large, randomised, double-blinded, placebo-controlled trial. We have selected a daily dose of 300 mg aspirin, as current evidence was derived from studies using this dose.

### Study objectives

The primary objective is to determine whether daily aspirin (300 mg) as an adjunct to compression improves the time to healing of the target ulcer in a 12-week treatment period.

The secondary objective is to determine the effects of aspirin on ulcer recurrence, wound pain, quality of life and wellbeing, adherence to study medication, adherence to compression therapy, serum inflammatory markers, hospitalisations, and adverse events at 24 weeks.

## Methods/design

### Study design

ASPiVLU is a randomised, double-blinded, multicentre, placebo-controlled, clinical trial to determine the clinical effectiveness of aspirin as an adjunct to compression in healing venous leg ulcers.

### Study setting and participants

The study population consists of adult patients living in Australia. The study is being conducted in four states (Victoria, New South Wales, Queensland, and Tasmania). Potential participants will be identified from community nursing settings, general practice clinics, and hospital outpatient wound clinics. All eligible patients will be identified at six participating ASPiVLU study wound clinics and offered study participation.

### Inclusion criteria

Inclusion criteria are as follows:Age 18 years and olderHave one or more leg ulcers in the presence of venous insufficiency confirmed by clinical assessment and/or duplex ultrasoundTarget ulcer (largest ulcer if more than one) is separated from the other ulcers by at least 1 cmTarget ulcer present for at least 6 weeks or has prior history of venous ulcerationTarget ulcer area ≥ 1 cm^2^ to ≤ 20 cm^2^ as measured by digital planimetry techniquesAnkle brachial pressure index (ABPI) measure of ≥ 0.7 mmHg *or* systolic toe pressure ≥ 50 mmHg to exclude arterial insufficiencyAble to provide informed consent (decision made according to the medical practitioner’s clinical judgement)

### Exclusion criteria

Exclusion criteria include the following:Current, daily aspirin useAspirin intoleranceAny existing condition or treatment that is a contraindication to aspirin therapy or to participate in the trial (decision made according to the medical practitioner’s clinical judgement)Concurrent use of any other antiplatelet or anticoagulation therapyPregnancy or breastfeeding

### Consent

Written information, in the form of a patient information and consent form, will be provided after verbal explanation of the research study. Patients will have the opportunity to discuss participation with research staff prior to enrolment. Written informed consent will be obtained from each participant prior to randomisation.

### Screening assessment

After giving consent, the patients will be screened at wound clinics to verify eligibility. Eligibility will be confirmed by the wound clinic doctor. Prior to randomisation, baseline data, including age, gender, smoking status, ethnicity and employment status, medical history and current medication use, will be recorded. A physical examination by a wound clinic consultant will include an assessment of the target ulcer, measurement of the wound surface area, and digital photography of the wound.

### Intervention

Study participants will be allocated to either active treatment with aspirin at a dose of 300 mg daily or inactive placebo. Study tablets are enteric-coated, un-scored, white tablets with identical appearance, provided by Bayer Pharma AG for the ASPiVLU trial. Participants will be advised to take one tablet each morning approximately half an hour before other medications to avoid potential drug interactions. Participants will continue to take the study medication daily for 24 weeks, regardless of whether or not the target ulcer heals.

### Compression therapy

All participants will be treated with compression therapy (the system of choice will be guided by clinician discretion and patient preference) for 12 weeks or until complete healing of the target ulcer occurs. Details of the compression type will be noted in the case report form. Once ulcer healing is achieved, the participants will be fitted with below-knee compression stockings that deliver between 23 mmHg to 32 mmHg compression at the ankle to prevent ulcer recurrence.

### Randomisation

Patients will be randomly assigned to aspirin or placebo via an electronic data capture system (EDC). The randomisation list will be generated by an independent statistician and implemented together with medication number selection by the database programmer. Randomisation codes will be allocated via a password-protected system.

### Allocation concealment and implementation

The study medication will be packaged in identical containers. Each container will be pre-labelled (by an independent drug-packaging group contracted to provide the study medication) with a study identifier according to the randomisation schedule. Allocation will be stratified by wound clinic and wound size as measured by the Margolis index [10]. The Margolis index is a prognostic score for venous ulcer healing derived from dichotomous categorisations of the ulcer area and duration of the current ulcer. Hence, stratification aims to avoid baseline imbalances in the ulcer size and duration, which are highly predictive of outcome. Stratification based on clinic site will avoid variance in any baseline characteristics related to the geographical location or local clinical practice. The study investigators and the research nurses distributing the medication and assessing outcomes will remain blind to the treatment allocation.

### Un-blinding

Un-blinding will occur in the event of a clinical emergency in which the knowledge of the medication taken is essential for the participant’s clinical management. The code can be broken by contacting the Trial Pharmacist via the ASPiVLU Trial Centre. Reasons for un-blinding will be recorded, and participants will be encouraged to resume their assigned medication, if possible, after their immediate condition has resolved.

### Primary outcome measure

The primary outcome is the time to healing of the target ulcer at 12 weeks after randomisation. Healing is defined as 100 % epithelialisation, with no exudate or scab. Proof of healing will be confirmed by an independent expert review of the digital photos of the ulcer. Time to healing will be measured in weeks from the date of randomisation.

The target ulcer is defined as the largest ulcer at baseline, which is separated from other ulcers by at least 1 cm and has a surface area between 1 cm^2^ and 20 cm^2^.

### Secondary outcome measures

The following secondary outcomes will be assessed in all participants at 24 weeks after randomisation.

#### Recurrence of target ulcer

Recurrence is defined as healed at 12 weeks and recurrence free at 24 weeks. After healing, the participants will be followed up to assess target ulcer recurrence. This will occur via monthly phone calls by the research staff from the date of healing to 24 weeks from randomisation.

#### Wound pain score

(Baseline and weekly until the wound is healed or to 12 weeks, whichever comes first, and then monthly via phone call until the study completion at 24 weeks): The participants’ self-reported assessments of pain associated with their VLUs in the past week will be measured with an 11-point (0–10) numerical rating scale, where a score of ‘0’ represents no pain, and ‘10’ represents the maximal pain imaginable.

#### Health-related quality of life and wellbeing index

(Baseline, 12 weeks, and 24 weeks): The EQ-5D is a health-related quality of life and wellbeing instrument. The EQ-5D-5 L is a widely used generic preference-based measure of health outcomes [23]. It consists of a descriptive system together with a visual analogue 0–100 scale. It assesses five dimensions of health – mobility, self-care, usual activities, pain/discomfort, and anxiety/depression. Participants are asked to rate each dimension as one of five levels (no problems, slight problems, moderate problems, severe problems, or extreme problems). This can result in 3125 (5^5^) possible health states, which can be converted to health utilities using nation-specific tariffs, which have been developed for a number of countries [24].

#### Adherence to study medication

(Weekly from baseline until healed or to 12 weeks, whichever comes first, and then monthly to 24 weeks from randomisation): Participants will be asked to self-report trial medication adherence and to present medication containers for pill counts at 24 weeks.

#### Adherence to compression treatment

(Weekly from baseline until healed or to 12 weeks, whichever comes first, and then monthly to 24 weeks from randomisation): Participants will be asked to report whether they adhered to wearing the compression on a categorical scale of ‘wear everyday’, ‘wear ≥ 3 days/week’, ‘wear ≤ 2 days per week’, and ‘do not wear’.

#### Adverse events

(Weekly until healed or to 12 weeks, whichever comes first, and then monthly via phone call until the study completion at 24 weeks): Adverse events will be elicited by open-ended questions and recorded in the adverse events log.

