#### Hospitalisation

At each contact, participants will be asked to report hospitalisation that occurs for any reason during the 24-week study period.

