**Fig. 1 Fig1:**
[figure not shown]
Schematic of the Aspirin in Venous Leg Ulcer trial (ASPiVLU) design

**Table 1 Tab1:** Study schedule

Measurement/activity	Screening^a^	Treatment period in weeks													Follow-up period	
		*(Weekly wound management and assessments until target ulcer healed OR 12 weeks – whichever occurs first. The 12-week visit is mandatory for all participants regardless of ulcer status.)*													*(from week 12 until week 24)*	
		Recruitment & Baseline Assessment (Day 1)	Wk 1	Wk 2^b^	Wk 3^b^	Wk 4^b^	Wk 5^b^	Wk 6^b^	Wk 7^b^	Wk 8^b^	Wk 9^b^	Wk 10^b^	Wk 11^b^	Wk 12	Monthly	Wk 24/end of study
Informed consent		X														
Eligibility criteria	X															
Recruitment & randomisation		X														
Target ulcer assessment – general features		X	X	X	X	X	X	X	X	X	X	X	X	X^3^		
Wound pain score		X	X	X	X	X	X	X	X	X	X	X	X	X^3^	X	X
Target ulcer assessment – size (tracing) & photo		X				X				X				X^3^		
Medical history including demographics & medications		X														
Physical examination including vital signs		X														
QOL assessment (EQ-5D-5L)		X												X		X
Serum sample		X												X		X
Trial medication dispensed		X														
Ulcer care education		X														
Adherence to compression (or hosiery)			X	X	X	X	X	X	X	X	X	X	X	X	X	X
Adherence to trial medication			X	X	X	X	X	X	X	X	X	X	X	X	X	X
Concomitant/new medication			X	X	X	X	X	X	X	X	X	X	X	X	X	X
Adverse events including hospitalisation			X	X	X	X	X	X	X	X	X	X	X	X	X	X
Wound assessment			X	X	X	X	X	X	X	X	X	X	X	X		
Ulcer prevention education			X^2^	X^2^	X^2^	X^2^	X^2^	X^2^	X^2^	X^2^	X^2^	X^2^	X^2^	X		
Target ulcer recurrence assessment															X^2^	X^2^
Refer to wound clinic														X^3^	X^4^	X^4^
Reconciliation of medication																X

^a^Screening to be conducted within 14 days of baseline (day 1) assessment

^b^Assessment conducted only if the target ulcer unhealed

X^2^ = if healed

X^3^ = if not healed

X^4^ = if ulcer has recurred *(this applies to participants whose target ulcer recurs after initial healing is achieved)*

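### Adverse-event, hospitalisation and medication-adherence questioning thins out once the ulcer heals while study drug continues, so ascertainment depends on the primary outcome and, if aspirin speeds healing, minor events on aspirin can be modestly under-counted

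*Protocol article*

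**What the plan says.** Under Adverse events, the protocol article gives the timing as "Weekly until healed or to 12 weeks, whichever comes first, and then monthly via phone call until the study completion at 24 weeks" and the method as "Adverse events will be elicited by open-ended questions and recorded in the adverse events log". Adherence to study medication follows the same weekly-then-monthly pattern, with a pill count at week 24. The Hospitalisation section says "At each contact, participants will be asked to report hospitalisation", so that outcome inherits whatever contact schedule applies.

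Table 1 has a row for "Adverse events including hospitalisation". Its week 2 to week 11 columns carry the footnote "Assessment conducted only if the target ulcer unhealed", and its Monthly column sits under a follow-up period defined as "from week 12 until week 24". The table also states: "The 12-week visit is mandatory for all participants regardless of ulcer status".

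Under Recurrence of target ulcer, follow-up after healing is described differently: "This will occur via monthly phone calls by the research staff from the date of healing to 24 weeks from randomisation".

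The Intervention section keeps all participants on daily study medication for 24 weeks irrespective of healing. Adverse events and hospitalisations are named secondary outcomes at 24 weeks, and the Discussion promises data on safety as well as efficacy.

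**The concern.** There are two linked problems.

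First, the passages disagree on what happens between healing and week 12. The Adverse events and Recurrence sections imply monthly calls from healing. Table 1 schedules nothing for a healed participant until the week-12 visit. On the table, a participant found healed at week 1 would go 11 weeks on study drug without being asked about adverse events. Sites cannot follow both.

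Second, on either version the frequency of questioning is set by healing, which the trial expects to differ between arms. Open-ended questions yield more when they are asked more often over shorter recall periods. If aspirin speeds healing, its participants spend more of their time on drug under sparse questioning. Blinding does not prevent this, because healing status and not knowledge of allocation drives the contact rate. Intention-to-treat analysis cannot restore events that were never elicited. The scenario affected is the one in which benefit has been shown and harms must be weighed against it.

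**Working it through.** **Inputs.** From Sample size: proportion unhealed at 12 weeks S12 = 0.5 (placebo) and 0.3 (aspirin), hazard ratio 1.74, 121 per group. From the sections above: week 1 and week 12 apply to all, weeks 2-11 only while unhealed. Assumed, not in the document: a constant healing hazard, and calls every 4 weeks where the text says monthly.

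**Check of the healing inputs.** ln(0.3)/ln(0.5) = 1.204/0.693 = 1.737, the stated 1.74. Freedman's formula at 90% power and two-sided 0.05 gives 145 events; 145/0.6/2 = 120.8, the stated 121 per group. The inputs are therefore those the trial planned on. The document gives no figure for contact frequency itself.

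**Hazards.** λ = -ln(S12)/12 = 0.0578 (placebo) and 0.1003 (aspirin) per week; S(t) = exp(-λt).

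**Enquiries in weeks 1-12, Table 1 reading.** The visit at week k (2 to 11) takes place if the ulcer was unhealed at visit k-1. Expected number = 1 + Σ S(k-1) for k = 2 to 11, + 1.
- Placebo: 1 + 7.38 + 1 = 9.38
- Aspirin: 1 + 6.00 + 1 = 8.00
- Ratio 8.00/9.38 = 0.853, about 15% fewer on aspirin.

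**Enquiries in weeks 1-12, calls from healing.** A participant found healed at weeks 1-3 gets two calls before week 12, and one found healed at weeks 4-7 gets one. Expected extra calls = [1 - S(3)] + [1 - S(7)].
- Placebo: 0.159 + 0.333 = 0.49, total 9.87
- Aspirin: 0.260 + 0.505 = 0.76, total 8.77
- Ratio 8.77/9.87 = 0.888, about 11% fewer on aspirin.

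**Over 24 weeks.** After week 12 both arms share one monthly schedule. Adding three common contacts (weeks 16, 20, 24):
- Table 1 reading: 12.4 v 11.0, about 11% fewer
- Calls from healing: 12.9 v 11.8, about 9% fewer

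**From contacts to events.** Mean unhealed time within 12 weeks = (1 - S12)/λ = 8.66 weeks (placebo) and 6.98 weeks (aspirin), leaving 3.34 and 5.02 healed weeks. Suppose sparse questioning captures a fraction c of what weekly questioning captures; c is not in the document, so a range is shown. The observed/true event rate ratio (aspirin:placebo) over weeks 0-12 is (6.98 + 5.02c)/(8.66 + 3.34c). For 24 weeks, 12c is added to numerator and denominator.

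| c | weeks 0-12 | weeks 0-24 |
|---|---|---|
| 0.5 | 0.92 | 0.95 |
| 0.7 | 0.95 | 0.97 |
| 0.9 | 0.99 | 0.99 |

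**The case against.** The best defence is that fewer contacts do not by themselves mean a biased comparison. A monthly question still covers the preceding month, the week-12 visit is compulsory for all, both arms are on the same schedule afterwards, and adverse events are an outcome at 24 weeks. All of this stands, and it is why the table above shows an attenuation of only 1-5% over 24 weeks. Even the 5% requires sparse questioning to miss half of the events.

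A reader might infer more: that aspirin's harms will be materially hidden, that hospitalisations will be under-counted, or that healed participants definitely go unasked until week 12. The documents do not support these readings. The direction of the differential depends on aspirin healing ulcers faster. A hospital stay is unlikely to be forgotten before the next contact. The long silence follows only from Table 1, which the text contradicts.

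It is also true that 37% of placebo and 55% of aspirin participants are expected to heal by week 8 (1 - S(8)), and so would wait at least 4 weeks for the next enquiry under Table 1. That is not a measure of harm, since a 4-week gap is also what a common monthly calendar would give everyone.

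Finally, the analysis of adverse events may properly be left to a statistical analysis plan that is not shown. That does not answer the point: the contact schedule is fixed here, and no analysis plan can recover information that was not collected.

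**Conclusion.** The concern holds in a limited form. Ascertainment of adverse events, hospitalisations and medication adherence depends on the primary outcome while exposure continues, and Table 1 conflicts with the text on contacts between healing and week 12. The conflict needs no assumption about efficacy. The imbalance does: at the planned healing rates and a constant hazard, aspirin participants have 11% to 15% fewer enquiries in weeks 1-12, depending on which version sites follow, and about 9% to 11% fewer over 24 weeks. The plausible consequence is a modest under-count on aspirin, mainly of minor and easily forgotten events. With equal healing there is no differential. A claim that the safety comparison is seriously distorted would go beyond what the documents show. Because the correction is cheap and the lost information cannot be recovered later, it should still be made.

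**What to change.** 1. Reconcile Table 1 with the Adverse events and Recurrence of target ulcer sections, so that one schedule governs contacts between healing and week 12.
2. Add common adverse-event, hospitalisation and medication-adherence contacts for all participants on a fixed calendar from randomisation, for example weeks 4, 8, 12, 16, 20 and 24. For healed participants these can be by phone, using the recurrence calls already planned, moved to calendar weeks.
3. At each common contact, ask everyone the same questions about the whole interval since the last common contact (or since randomisation), whether or not an event has already been logged.
4. Keep all recorded events in the main safety report. Add, as a sensitivity analysis, a between-group comparison of non-serious events based on the common-contact questions.

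Events should not be excluded merely because they were first reported at a weekly visit. Unhealed participants, expected more often on placebo, may not repeat a logged event unless asked again, so dropping those events could reverse the bias. Step 3 guards against this.

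The cost is at most two short calls before week 12 (weeks 4 and 8) for early healers, some repeat questioning of unhealed participants, and a correction to the table. Treatment is not affected.
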